### Study purpose

Our primary outcomes are to assess whether the intergenerational HOW R U? intervention (1) reduces SIL more than the waitlist control group at study week 12 and (2) reduces SIL more than the current same-generation peer support HOW R U? intervention at study week 12.

Secondary outcomes include assessing:The impact of the intergenerational HOW R U? intervention on (i) SIL at study week 24, (ii) depression, (iii) quality of life, (iv) functional status, (v) generativity, (vi) participant’s perceived self-benefit, and (vii) participant’s perceived benefit for the volunteer delivering the HOW R U? intervention at study weeks 12 and 24.Participant stated preferences for intergenerational versus same-generation peer support HOW R U? intervention prior to randomization. Note, participants will be randomized regardless of their intervention preference.

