Key inclusion and exclusion criteria	Inclusion Criteria 1. Community-dwelling person 70 years of age and older receiving care from the ED, Family Medicine or Geriatric clinics at the two participating sites (MSH, NYGH) 2. Baseline de Jong loneliness score of 2.0 will be required for participating in the trial Exclusion Criteria 1. Age less than 70 years of age 2. Patients with communication problems (critically ill, unconscious, language barrier, speech impairment or otherwise unable to provide consent) or admission to a hospital for greater than 72 h) 3. Patients with severe cognitive impairment or those with living in nursing homes who are dependent on others for their activities of daily living 4. Patients without any mobile phone or landline Volunteer Inclusion Criteria 1. Peer-support volunteers will be 60 years of age or older 2. Intergenerational volunteers will be between 19–39 years of age
Study type	Interventional Allocation: Randomized interventional model. Parallel assignment. Outcome assessor masking Primary purpose: Supportive Care
Date of first enrolment	November 1, 2021
Target sample size	141
Recruitment status	Recruiting
Primary outcome(s)	1. Change in loneliness using De Jong Gierveld 6-item Loneliness Scale from baseline to 12 weeks
Key secondary outcomes	1. Change in loneliness using De Jong Gierveld 6-item Loneliness Scale from baseline to 24 weeks 2. Change in perceived social support using Lubben Social Network Scale from baseline to 12 and 24 weeks 3. Change in mood using Geriatric Depression Scale from baseline to 12 and 24 weeks 4. Change in baseline cognition using “Brief Alzheimer’s Screening Test” from baseline to 12 and 24 weeks 5. Change in Quality of Life using Euro-Qual 5 Dimensions 5 Levels from baseline to 12 and 24 weeks 6. Change in Functional Status using Older Americans Resource Scale from baseline to 12 and 24 weeks 7. Change in self-perceptions of generativity using Loyola Generativity Scale from baseline to 12 and 24 weeks 8. Perceived benefit to participant at 12 and 24 weeks 9. Perceived benefit to volunteer at 12 and 24 weeks

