### Outcome measures

The primary outcome is loneliness as measured using the six-item De Jong loneliness scale after completion of the intervention (weeks 12–14 of the study). The De Jong scale has been extensively validated in older populations and is divided into four clinically relevant categories: 6—severe loneliness, 4–5—moderate-to-severe loneliness, 2–3—low loneliness, and 0–1—no loneliness [12].

The secondary outcomes are the following: (1) the de Jong loneliness Scale at 12 weeks post-completion of the intervention to assess sustainability (study week 24); (2) six-item Lubben’s Social Network Scale [18]; (3) five-item Geriatric Depression Scale to assess mood [19]; (4) Brief Alzheimer’s Screening Test to assess baseline cognitive performance [20]; (5) EQ-5D-5L to assess perceived health-related quality of life in the areas of self-care, mobility, usual activities, pain/discomfort, and anxiety/depression [21]; (6) the Older Americans Resource Scale to assess functional status [22]; (7) the Loyola Generativity Scale to assess generativity [23]; (8) perceived benefit by the participant; and (9) benefit to the volunteer as perceived by the participant. The standardized measurement instruments selected for the trial have been extensively validated in older adults. The Loyola Generativity Scale has demonstrated good interrater reliability as well as responsiveness in trials of older adults [24, 25]. To assess the secondary outcome of participant preference for same-generation peer support versus intergenerational HOW R U? intervention, we will use a 5-point Likert scale with the following options: “I strongly prefer peer support,” “I prefer peer support,” “neutral,” “I prefer intergenerational,” and “I strongly prefer intergenerational”. Please see Appendix 3 for full details.

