### Analysis

All analyses will use SAS Version 9.4 (SAS Institute, Cary, NC, USA). A two-sample two-sided test of proportions will be used to assess the primary outcome of loneliness in the control group versus the intergenerational HOW R U?, and the control group versus the same-generation peer support HOW R U? intervention. Improvements in the binary outcome of the loneliness category of the De Jong Loneliness Scale will be assessed using a logistic regression model, and results will be reported as odds ratios with the corresponding 95% confidence intervals. The variance inflation factor (VIF) will be calculated to assess for multicollinearity before the logistic regression model is built such that if two variables are highly correlated (i.e., VIF > 4 or tolerance < 0.25), only one of the two variables is retained for the final model. To compare the secondary outcomes, they will be reported as means with corresponding 95% confidence intervals.

Potential missing data will be managed as follows. For logistic regression, participants with more than 15% missing data for confounding variables will be excluded from the analysis. Note that in the main trial, less than 5% of participants would have been excluded. For participants with less than 15% missing data, we will use imputation for confounding variables. Participants with missing outcome data will be excluded from analysis (i.e., lost to follow-up). Note that after two-thirds of the participants have been enrolled, we will assess the loss-to-follow-up rate and adjust the enrollment accordingly. For example, if the lost-to-follow-up rate is 20%, we will increase the enrolment by 20%. To manage protocol nonadherence, participants will be analyzed using intention-to-treat analysis regardless of their adherence to the protocol.

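### The primary outcome is stated in three forms with two analyses and no deciding one, and the category form gives up efficiency that a baseline-adjusted 0–6 score would keep

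*Protocol article*

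**What the plan says.** Four places in the protocol article bear on the primary outcome.

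- **Study purpose** words the first aim as whether the intervention "reduces SIL more than the waitlist control group at study week 12".
- **Table 2, primary outcome** (under Methods/design): "Change in loneliness using De Jong Gierveld 6-item Loneliness Scale from baseline to 12 weeks". This is a change score.
- **Outcome measures**: "loneliness as measured using the six-item De Jong loneliness scale after completion of the intervention", at weeks 12–14. This is a follow-up level. The same section gives the categories: "6—severe loneliness, 4–5—moderate-to-severe loneliness, 2–3—low loneliness, and 0–1—no loneliness".
- **Sample size and power** and **Analysis**: the proportion who improve by a category. This is a responder rate.

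The Analysis section offers two methods. First: "A two-sample two-sided test of proportions will be used to assess the primary outcome of loneliness". Next: "Improvements in the binary outcome of the loneliness category of the De Jong Loneliness Scale will be assessed using a logistic regression model". The logistic model carries confounding variables that are not named. Where two of them are highly correlated on the variance inflation factor (VIF), "only one of the two variables is retained for the final model"; which one is kept is not stated. Under Randomization and blinding, allocation is stratified by referral source.

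**The concern.** A change score, a follow-up level and a responder rate are different quantities and can disagree. With two analyses and no ranking, the deciding result could be picked after the data are seen. The two analyses need not even use the same participants: those with more than 15% missing confounder data leave the logistic model, and no such exclusion is stated for the test of proportions.

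The responder definition adds its own problem. Whether a one-point change counts depends on the exact starting score, so chance imbalance in baseline scores feeds into the responder rate. The test of proportions corrects neither for that nor for the stratification factor. Collapsing a seven-level score to yes or no may also cost power that the collected data could supply.

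**Working it through.** **1. The forms can point in opposite directions.** Suppose everyone starts at 4. In arm X half go to 3 and half go to 6. In arm Y all stay at 4. Responders are 50% in X and 0% in Y, which favours X. The mean change is (−1 + 2)/2 = +0.5 in X and 0 in Y, and the mean level is 4.5 against 4.0; both favour Y. The example is extreme, but it shows that the choice of form is not cosmetic.

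**2. The category rule.** The cut-points are 0–1, 2–3, 4–5 and 6, and entry requires a score of at least 2.

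| One-point fall | Crosses a category? |
|---|---|
| 6 to 5 | yes |
| 5 to 4 | no |
| 4 to 3 | yes |
| 3 to 2 | no |
| 2 to 1 | yes |

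Worsening scores the same as no change. The sample-size text does not say whether a fall of several categories counts, that is, whether it means at least one category.

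**3. Reproducing the plan's figure.** Inputs from Sample size and power: control rate 15%, difference 28.1 points (so 43.1% in the treated arm), 47 per arm, power above 80%. Two-sided alpha is not stated; 0.05 is assumed from the 95% confidence intervals.

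- Mean proportion: (0.15 + 0.431)/2 = 0.2905.
- n = [1.96·√(2·0.2905·0.7095) + 0.8416·√(0.15·0.85 + 0.431·0.569)]² / 0.281² = (1.2584 + 0.5138)² / 0.07896 = 39.8, so 40 per arm.
- With continuity correction: (39.8/4)·[1 + √(1 + 4/(39.8·0.281))]² = 46.6, so **47 per arm**. This matches the plan.
- Power at 47 per arm: 80.4% with continuity correction, 86.3% with the pooled normal test, 81.9% with Fisher's exact test.

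The stated power therefore holds at the upper end of the range. The lower end (13.9 points) depends on a control rate that is not given, and this point does not need it.

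**4. What the category coding costs.** The documents give neither an SD nor a baseline-to-follow-up correlation, so both are assumed. The model has baseline scores spread evenly over 2 to 6. The follow-up score is linear in baseline with normal error, rounded and limited to 0–6. Shifts are set so that 15% of controls improve a category and the treated arm reaches the target rate. There are 47 per arm, two-sided 0.05, and 1,200 simulated trials per row (simulation error about 1 to 1.4 points where power is 60–86%). Entries are power in %.

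| SD, correlation | Treated rate | Test of proportions | Logistic + baseline | Unadjusted score (rank test) | ANCOVA on score |
|---|---|---|---|---|---|
| 1.5, 0.5 | 43.1% | 86.5 | 90.8 | 98.3 | 99.9 |
| 1.5, 0.7 | 43.1% | 87.3 | 88.2 | 89.0 | 99.2 |
| 2.0, 0.5 | 43.1% | 86.3 | 86.2 | 94.2 | 98.4 |
| 2.0, 0.7 | 43.1% | 84.3 | 83.5 | 80.5 | 97.8 |
| 1.5, 0.5 | 35% | 64.3 | 67.8 | 89.1 | 95.8 |
| 1.5, 0.7 | 35% | 59.4 | 61.7 | 69.8 | 92.9 |
| 2.0, 0.5 | 35% | 62.5 | 62.0 | 75.5 | 87.3 |
| 2.0, 0.7 | 35% | 57.3 | 57.0 | 55.2 | 81.1 |

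At 40% improving, the test of proportions has 79–80% and ANCOVA 95–99%. Across all these scenarios, adding baseline to the binary model moves power by only about −1 to +4 points. The reliable gain comes from using the score and the baseline together.

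**The case against.** The strongest reply is that category improvement is a legitimate endpoint. Outcome measures calls the categories clinically relevant, the trial was sized on them, and the sample size and the test of proportions agree with each other. Making category improvement primary everywhere would cure the ambiguity equally well. This stands: the inconsistency has to go, but the score is a recommendation and not the only remedy. It also stands that a change of endpoint during recruitment is more than an edit of wording.

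Three stronger readings are tempting, and the documents do not support them.

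- *The plan ignores baseline.* The responder is defined against each participant's own baseline category, and the unnamed logistic covariates could include baseline score and referral source. The covariate list may sit in a fuller document. Only the test of proportions is plainly unadjusted.
- *The plan tests the weakest of its three forms.* This is false in general. In the table, the unadjusted follow-up score is weaker at SD 2.0 and correlation 0.7 (80.5% against 84.3%). In a separate simulation of a 1.0-point effect (assumed mean 3.5, SD 2), the test of proportions against the unadjusted score had 67% against 75% at correlation 0.7, but 80% against 76% at 0.8 and 93% against 81% at 0.9.
- *The stated power is wrong.* It reproduces at 28.1 points.

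The size of the loss can also be challenged, because it rests on assumptions. Without forcing control improvement to 15%, models of this kind often give more (about 19–32% at correlations of 0.7–0.8), which departs from the plan's premise. The table fixes the rate at 15% for that reason. No figure can be given for leaving out referral source.

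**Conclusion.** The point holds as a stated contradiction plus lost efficiency. The article gives three forms of the primary outcome and two analyses without saying which decides. That can change the trial's conclusion, and an unseen analysis plan could agree with only one of the three forms. The asymmetry of the category rule follows directly from the published cut-points.

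The efficiency loss is real but conditional. With SD 1.5–2.0, correlation 0.5–0.7 and 15% control improvement, the baseline-adjusted score has about 98–99.9% power against 84–87% at the planned effect, and 81–96% against 57–64% at 35% improving. The direction is consistent across the scenarios; the exact size cannot be derived from the documents. The need for one endpoint and one deciding analysis does not depend on any of these power figures.

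**What to change.** State one primary endpoint and one deciding analysis in the same terms in Table 2, Outcome measures, Sample size and power, and Analysis.

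*Preferred:* the De Jong 0–6 score at weeks 12–14, analysed by ANCOVA or a proportional-odds model with arm, baseline De Jong score and referral source. In ANCOVA with baseline as a covariate, the arm effect is the same whether the response is the follow-up score or the change, so this also serves the Table 2 outcome. Keep improvement by at least one category as a supportive logistic analysis with the same covariates.

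*If category improvement stays primary:* define it as at least one category, and make the logistic model adjusted for baseline score and referral source the deciding analysis. Fix those covariates in advance and exempt them from the VIF rule. The power gain is then small, but the ambiguity is gone.

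*Cost:* no extra participants or data. Under the preferred option the headline becomes a mean difference or common odds ratio in place of a percentage improved, and the sample-size text would describe the supportive endpoint and should say so. Recruitment began in November 2021 according to Trial status, so the change must be made and dated before anyone sees unblinded outcome data.

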### Sample size and power

Each group will consist of a sample of 47 subjects which will detect a 13.9–28.1% difference between the treatment and control groups in the proportion of people who improve by one category (e.g., from severe loneliness to moderate-to-severe loneliness) with a power greater than 80%. This assumes that up to 15% of control group participants may have a spontaneous improvement in loneliness categories. With these sample sizes, three comparisons may be made: intergenerational intervention to the control group, same-generation peer support intervention to the control group, and intergenerational to the same-generation peer support intervention.

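### The primary outcome is sized and tested as a difference in proportions but reported only as a logistic odds ratio, which is infinite or unstable if very few controls improve

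*Protocol article*

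**What the plan says.** Three statements in the protocol article bear on this.

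- **Sample size and power.** "Each group will consist of a sample of 47 subjects", and this number "will detect a 13.9–28.1% difference between the treatment and control groups" in the proportion improving by one loneliness category, "with a power greater than 80" per cent. The control rate is given only as a ceiling: "up to 15% of control group participants may have a spontaneous improvement". Neither a lower control rate nor an alpha is printed.
- **Analysis, the test.** "A two-sample two-sided test of proportions will be used to assess the primary outcome of loneliness", for each intervention arm against control.
- **Analysis, the estimate.** Improvement in loneliness category is also assessed by logistic regression, and "results will be reported as odds ratios with the corresponding 95% confidence intervals". The interval type is not named. No difference in proportions with an interval is promised for the primary outcome.

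**The concern.** The sizing and the test share one scale, and the promised estimate is on another. At moderate control rates this is harmless. At very low ones it is not. If no control participant improves, the maximum-likelihood odds ratio is infinite and has no usable Wald interval. If one or two improve, a Wald interval is very wide.

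The lower limit of the printed detectable range appears to have been calculated at just such a rate. The trial could then reject on its primary test and have no usable figure for the size of the effect. An estimator would have to be chosen after the data were seen.

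**Working it through.** **Inputs.** From the article: n = 47 per arm, two-sided test of proportions, control rate up to 15%, detectable difference 13.9 to 28.1 points, power above 80%, 95% CI for the odds ratio. Assumed: the alpha used for sizing, the lower control rate, the interval type, and no covariates.

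**Step 1: reproduce the printed range.** For x control and y treated improvers, z = [(y − x)/n] / √[p̄(1 − p̄)·2/n], with p̄ = (x + y)/(2n). Power is the sum of the two binomial probabilities over all 48 × 48 tables in which |z| exceeds the critical value. Solving for the difference that gives 80% power:

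| Two-sided alpha | Control 0% | Control 15% |
|---|---|---|
| 0.05 | 11.4 points | 25.2 points |
| **0.025** | **13.89 points** | **28.11 points** |
| 0.0167 | 16.3 points | 29.7 points |

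Only 0.025 matches both printed limits. The lower limit can be checked by hand. For 0 v 5 improvers, p̄ = 5/94 = 0.0532 and z = 0.1064/0.0463 = 2.30, above the critical value of 2.24. For 0 v 4, z = 2.04, which is below it. With 0% control improvement the power is therefore the chance of at least 5 treated improvers in 47, and this is 80% at a treated rate of 13.89%.

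If alpha was 0.05 instead, 13.9 points has at least 80% exact power only at control rates up to about 1.3%. Either way, the printed lower limit implies control improvement near zero.

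**Step 2: how often the odds ratio is infinite.** P(no control improvers) = (1 − p)^47. At p = 0.02 this is 0.98^47 = 0.39.

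**Step 3: power of the odds ratio analysis.** The difference at each control rate is the one at which the z-test has 80% power at alpha 0.025. The Wald statistic is ln(OR)/√(1/x + 1/(n−x) + 1/y + 1/(n−y)), and tables with an empty cell count as non-significant. Both logistic columns use the 95% level that the article prints.

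| Control rate | Difference (points) | P(no control improvers) | Wald 95% CI excludes 1 | Likelihood ratio, 5% level |
|---|---|---|---|---|
| 0% | 13.9 | 100% | 0% | 96.7% |
| 1% | 16.8 | 62% | 21.7% | 92.1% |
| 2% | 18.5 | 39% | 43.1% | 90.2% |
| 5% | 22.0 | 9% | 75.8% | 88.1% |
| 6% | 23.0 | 5% | 80.2% | 88.2% |
| 7.5% | 24.3 | 3% | 84.0% | 88.5% |
| 10% | 26.0 | 0.7% | 86.3% | 88.5% |
| 15% | 28.1 | 0.05% | 86.6% | 87.7% |

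The Wald shortfall ends at a control rate of about 6%.

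**Step 4: can the test and the interval disagree?** With the test at 0.025 and a 95% Wald interval, no table free of empty cells has a significant test in favour of treatment and an interval covering 1. With the test at 0.05, ten such tables exist. An example is 1 v 7 improvers:

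- z-test p = 0.027
- OR = (7/40)/(1/46) = 8.05
- SE of ln(OR) = √(1 + 1/46 + 1/7 + 1/40) = 1.09
- 95% CI = exp(2.086 ± 1.96 × 1.09) = 0.95 to 68

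At the differences giving 80% power at 0.05, these tables together have probability 13% at a 2% control rate, 5% at 5%, 1% at 10% and 0.5% at 15%.

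**The case against.** The case against is substantial, and most of it stands.

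- **A reader might infer that the power claim is false.** It is not. The power is stated for a difference in proportions, and the named primary test is a test of proportions. An accompanying logistic model need not carry that power.
- **A reader might infer that a logistic odds ratio is underpowered as such.** The loss belongs to the Wald interval, which the article does not specify. The score test from the unadjusted logistic model is the pooled z-test itself, and the likelihood-ratio test keeps above 80% throughout. That advantage is partly because it is liberal at some low rates, with a type I error of about 9% when both rates are 5%. Interval type is also something an article may leave to a fuller document, so its absence is not the point here.
- **A reader might infer that the plan's test and interval contradict each other.** At the alpha that reproduces the printed range they do not, apart from tables with no control improver, where no Wald interval exists. Disagreement otherwise needs the test to be run at 0.05.
- **A 0% control rate is inferred, not printed.** It is the edge of a range. At the only printed rate, 15%, an empty control cell is very unlikely and even a Wald interval has about 87% power for 28.1 points.
- **The difference of scale alone is mild.** At 15% v 43.1% the odds ratio is (0.431/0.569)/(0.15/0.85) = 4.29. It and the 28.1 points follow from the same two proportions, and nothing says that group proportions will be withheld.

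What these arguments do not remove is that the estimate the article commits to is infinite whenever no control improves, whatever interval is used, and that the printed 13.9 points reproduces only near that situation.

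**Conclusion.** The point holds in a limited form. The primary outcome is sized and tested on one scale, and the only effect estimate promised is on another, where it fails at the low end of the plan's own range. The problem matters for control improvement below about 6%. At 2%, the odds ratio is infinite in 39% of trials because no control improves, and a Wald 95% interval would have about 43% power where the z-test has 80%. From about 7.5% control improvement upward there is no material shortfall.

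This rests on the inferred alpha of 0.025, a lower control rate of 0% read from the printed range, Wald intervals for the power figures, and no covariates. The infinite odds ratio with 0 of 47 controls improving needs none of the first three assumptions. Covariate adjustment was not modelled. At the lower design point only about 47 × 0.139 = 6.5 improvers are expected across two arms, which gives an adjusted model little information. This is an improvement to consider, not an error that invalidates the plan.

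**What to change.** In the Analysis section, state that the effect estimate accompanying the primary test is the difference in proportions with a score-type 95% CI (Miettinen-Nurminen or Newcombe). This is on the same scale as the test and the sizing, and it remains finite when no control improves. Keep the logistic model as supporting analysis, fitted with Firth's penalty and profile-likelihood limits so that the odds ratio stays finite.

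The cost is two sentences and standard software options, with no extra participants or data. The downside is slight shrinkage of the odds ratio toward 1. The change should be made before outcome data are analysed, so that the estimator is not chosen after the number of control improvers is known.

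### No alpha is stated, the detectable range appears to assume 0.025 per comparison while the analysis reports 95% intervals without a split or order, and the sections disagree on which contrasts are primary

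*Protocol article*

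**What the plan says.** **Sample size and power.** The arms have 47 participants each. The article claims that this number "will detect a 13.9–28.1% difference between the treatment and control groups". The endpoint is improvement by one loneliness category, and the claim is made "with a power greater than 80" per cent. On the control arm, the assumption reads: "up to 15% of control group participants may have a spontaneous improvement in loneliness categories". No alpha is given. The section ends: "With these sample sizes, three comparisons may be made", and lists all three pairwise contrasts.

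**Analysis.** "A two-sample two-sided test of proportions will be used to assess the primary outcome of loneliness", for two contrasts: control versus intergenerational, and control versus peer support. A logistic model follows, whose "results will be reported as odds ratios with the corresponding 95% confidence intervals". No alpha, split, order or gatekeeping rule is given.

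**Study purpose and Hypotheses.** The two primary questions are whether the intergenerational arm does better than the waitlist and whether it does better than peer support. Peer support versus waitlist is not among them.

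**The concern.** A reader cannot tell at what level a comparison will be declared positive, or which comparisons carry the primary claim. The sample size seems to have been worked out at a stricter level than the 95% intervals imply. If the comparisons are judged at 0.05 each with no order, the chance of at least one false primary claim exceeds 5%.

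The three descriptions of the family make this worse. One contrast that the aims call primary (intergenerational versus peer) has no primary test, and one that the aims do not name (peer versus control) has one. With the level and the family both open, either could be settled after results are known.

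**Working it through.** **Inputs.** From Sample size and power: n = 47 per arm, stated differences 13.9 and 28.1 points, power 80%, control improvement up to 15%. From Analysis: two-sided two-sample test of proportions. Assumed here: the lower control rate is 0%, and the test is the pooled z-test without continuity correction.

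**Formula.** With a and b improvers in two arms of n, z = |b − a|/n ÷ √[p̄(1 − p̄)·2/n], where p̄ = (a + b)/(2n). Power is the sum of the two binomial probabilities over all (a, b) with z at or above the critical value: 1.960 for alpha 0.05, 2.241 for 0.025.

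**Reproducing the lower limit by hand.** With a 0% control rate, a = 0 always.
- b = 4: p̄ = 4/94, z = 2.04. This rejects at 0.05 but not at 0.025.
- b = 5: p̄ = 5/94, z = 2.30. This rejects at 0.025.

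So at 0.025 the power at 13.9% is P(X ≥ 5) with X ~ Bin(47, 0.139) = 0.801. At 0.05 it is P(X ≥ 4) = 0.907.

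**Both limits, by full enumeration with n = 47.**

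| Two-sided alpha | Detectable at 80%, control 0% | Detectable at 80%, control 15% | Power, 0% vs 13.9% | Power, 15% vs 43.1% |
|---|---|---|---|---|
| 0.05 | 11.4 | 25.2 | 0.907 | 0.871 |
| 0.025 | 13.89 | 28.11 | 0.801 | 0.800 |

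The 0.025 row matches both stated limits, and 0.025 = 0.05/2.

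**Other routes to the stated range.**
- Normal approximation: 15.1–25.6 at 0.05, and 17.9–28.5 at 0.025.
- Fleiss continuity correction at 0.05: 18.9–28.1. Only the upper limit fits.
- Fisher's exact test at 0.05: 16.3–27.4.
- Arcsine formula with a 0.5% control rate: 13.9 and 28.1, again at 0.025.
- Exact pooled z-test at 0.05 with 38 per arm: 14.0–28.3, a near match.

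**Family-wise error under the global null.** Three equal arms, z statistics for each pair (correlation ±0.5 between pairs sharing an arm), 3 million draws:

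| Level per test | Two contrasts sharing an arm | All three pairwise |
|---|---|---|
| 0.05 | 9.0% | 12.2% |
| 0.025 | 4.6% | 6.4% |

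**Which contrasts are primary, by section.**

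| Section | Intergenerational vs waitlist | Intergenerational vs peer | Peer vs waitlist |
|---|---|---|---|
| Study purpose, Hypotheses | yes | yes | no |
| Sample size and power | allowed | allowed | allowed |
| Analysis (test of proportions) | yes | no | yes |

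**The case against.** **The 0.025 is reverse-engineered.** This stands as a caveat. The match needs exact enumeration and a 0% lower control rate, which the article does not state. The near match at 0.05 with 38 per arm corresponds to 47 less the 20% loss that the Analysis section uses as an example (47 × 0.8 = 37.6). Against that reading, the section says enrolment would be raised to offset loss, and the fit is within 0.2 points rather than exact. The 0.025 reading fits better, but it remains an inference.

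**The 95% intervals may be only a reporting convention.** This also stands in part. They are attached to the logistic odds ratio, and no sentence says that each test is run at 0.05. If a split was planned and left out of the article, the error is 4.6% for two contrasts. A reader might infer that the trial has a 9–12% false-positive rate as a matter of fact. The document does not support that: the figure is conditional on unadjusted testing at 0.05, and the three-contrast figure also requires that a permissive sentence be read as a primary family of three.

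**The power statement is true.** Correct. A reader might infer that the trial is underpowered because a three-way split (alpha 0.0167) would cut power at the stated differences to 65% and 75%. No section proposes that split, so those figures describe no planned analysis.

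**Multi-arm trials need not always adjust, and the rule may sit in an unseen analysis plan.** Adjustment is debatable in general. Here, however, two claims about one arm form a single primary hypothesis, and the sample size itself appears adjusted. An analysis plan could supply the alpha; it would not remove the conflict between this article's own sections over the primary contrasts.

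**Conclusion.** The point holds as an inconsistency and an omission, not as a proven inflated error rate. The firm part is that the sections contradict each other on the primary family, that intergenerational versus peer has no stated primary test, and that no alpha or order accompanies the 95% intervals. The inferred part is that the sample size used 0.025 per comparison.

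The size depends on how the gap is filled: 9.0% (two contrasts) or 12.2% (three) if each is tested at 0.05; 4.6% or 6.4% at 0.025. These figures assume equal arms, large-sample z statistics and no true differences. Power at the stated differences is about 80% at 0.025 and 91% and 87% at 0.05, so 47 per arm remains justified either way for the comparisons with control.

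**What to change.** 1. Reconcile Study purpose, Hypotheses, Sample size and power, and Analysis so that the primary family is intergenerational versus waitlist and intergenerational versus peer. Add the missing primary test of the second contrast.
2. Choose one rule and state it: (a) test both at two-sided 0.025 (Bonferroni) with 97.5% intervals, the level the sample size appears to use; or (b) a fixed sequence, waitlist contrast first and then peer, each at 0.05 with 95% intervals. Holm should not be paired with fixed 97.5% intervals, because its second step is at 0.05 and the interval could then contradict the test.
3. Label peer support versus waitlist as secondary, outside the family.
4. State the alpha, and the control-rate range behind the two limits, in the sample-size paragraph.

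**Cost.** Wording only; the sample size does not change. Under (a), a p-value between 0.025 and 0.05 no longer counts as positive. Under (b), the peer contrast cannot be claimed if the waitlist contrast fails. The change should be dated before the data are analysed.
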